
**Figure 1 figure1:**
[figure not shown]
Randomized controlled trial flow diagram. Tx: Treatment.

### Randomization and Blinding

Block randomization of eligible participants will be performed to form the LEV, PER, and placebo groups. Blinding of participants, clinicians, and data collectors will be performed so that these individuals do not have access to group assignment details (Figure 2). Before accepting the case, the pharmacist, who is a nonresearch team member, sets the blocks and determines the distribution of random numbers using a random number table. The pharmacist is responsible for conducting all phases of the research. Additionally, the 3 topic groups can be equally distributed among participants through random assignment.

**Figure 2 figure2:**
[figure not shown]
SPIRIT flow diagram: schedule of enrollment, interventions, and assessment procedures. EEG: electroencephalography; MRI: Magnetic Resonance Imaging; mRs: modified Rankin Scale; NIHSS: National Institute of Health Stroke Scale; SPIRIT: Standard Protocol Items: Recommendations for Interventional Trials; TEAE: treatment-emergent adverse event; **: primary outcome; *: secondary outcome.

### Procedure and Assessment

We will document patients with initial NIHSS scores of >8 [40]. For reperfusion therapy, we will also use a modified Rankin scale for treatment evaluation [43]. For each participant, we will use brain MRI to confirm MCA territory infarction and exclude that of other territories and lacunar infarction. The MRI image depicting the typical case with an MCA infarct enrolled in this study is displayed in Figure 3. Baseline EEG during admission prior to AED administration will be arranged to exclude patients with early or concurrent clinical or electrographic seizures (Figure 2).

**Figure 3 figure3:**
[figure not shown]
A typical case with middle cerebral artery infarct enrolled in this study.

### Outcome Measures

#### Primary Outcome

The primary outcome measure will be the incidence of poststroke epilepsy and seizure severity at the end of the study period. Univariate ANOVA of the LEV, PER, and placebo groups will be performed. Intention-to-treat analysis will be performed. Participants will be followed up 1, 3, 6, 9, 12, and 18 months after stroke. If a seizure occurs during the prophylactic medication administration period, individual unblinding and adjustment of AEDs will be implemented. If a seizure occurs after the prophylactic medication administration period, ordinary medical care will be provided. We will record seizure type and duration after stroke onset at seizure occurrence **(**Table 1 and Figure 2).

**Table 1 table1:** Summary of follow-up visits.

Visiting time	Within 3 days	3 months	6/9/12 months	18 months
NIHSS^a^	✓			
mRs^b^	✓			✓
MRI^c^	✓			
EEG^d^	✓			
Start of medication	✓			
TEAE^e^	✓	✓		
Occurrence of seizure	✓	✓	✓	✓
Occurrence of death	✓	✓	✓	✓

^a^NIHSS: National Institute of Health Stroke Scale.

^b^mRs: modified Rankin scale.

^c^MRI: magnetic resonance imaging.

^d^EEG: electroencephalograph.

^e^TEAE: treatment-emergent adverse event.

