**Methods:**

Participants with MCA infarction, either with or without reperfusion treatments, will be recruited and promptly receive preventive intervention within 72 hours of the stroke occurrence. These participants will be randomly assigned to receive either PER (4 mg per day), LEV (1000 mg per day), or a placebo that matches the active drugs. This treatment will continue for 12 weeks after allocation. Brain magnetic resonance imaging will be used to confirm the presence of MCA territory infarction, and an electroencephalography will be used to ensure the absence of epileptiform discharges or electrographic seizures at the time of the stroke. All participants will undergo follow-up assessments for 72 weeks after allocation.

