**Results:**

The primary outcome under evaluation will be the incidence of poststroke epilepsy in the 3 groups following the 18-month study period. Secondary outcomes will encompass the time to the occurrence of the first seizure, the severity of seizures, any treatment-related adverse events, and the modified Rankin scale score at 3 and 18 months. Exploratory outcomes will involve comparing the effectiveness and safety of PER and LEV.

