**Conclusions:**

We anticipate that the intervention groups will experience a lower incidence and reduced severity of poststroke epilepsy compared to the control group after 18 months. We aim to establish evidence supporting the potential preventive effects of LEV and PER on poststroke seizures and epilepsy in patients with MCA infarction, as well as to explore the antiepileptogenic potential of both LEV and PER in patients with major ischemic strokes.

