### Concept of Epileptogenesis

Antiepileptic drugs (AEDs) or antiseizure medications may prevent the recurrence of seizures but do not cure epileptogenesis. An epileptogenesis is the process by which the previously normal brain is functionally altered and biased towards the generation of abnormal electrical activity that induces chronic seizures [17]. It involves molecular, anatomical, or circuit-level alterations, such as cell death or dysregulation of an ion channel or neurotransmitter receptor and the impairment of intrinsic plasticity. How these different levels of alteration are regulated remains unclear. Studies have reported that the epigenetic factor chromodomain Y-like protein, a critical regulator of the initiation and maintenance of intrinsic neuroplasticity that works by regulating voltage-gated sodium channels [18], is involved, and epileptic neurons may also develop short- and long-term adaptive changes in sensitivity to gamma-aminobutyric acid (GABA)ergic neurotransmission [19], worsening excitatory or inhibitory imbalance and thus reducing the possibility of successful therapeutic approaches using traditional AEDs. Further, an increasing amount of research, including ours, suggests a major involvement of inflammation in epileptogenesis [20-22]. Seizure activity elicits the release of proinflammatory cytokines and activates immune responses.

We have studied medications with potential antiepileptogenesis effects in pilocarpine-induced seizure animal models, supporting the concept of antiepileptogenesis with intervention immediately following brain insult [21-23].

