The three groups are described as follows, and the study flowchart is shown in Figure 1: (1) For the control group, a placebo will be administered to patients, and we will maintain standard stroke care during hospital admission if no acute seizure occurs during this period. If an acute seizure occurs, unblinding will be performed, and we will administer AEDs not including LEV or PER; the patient will be maintained on these AEDs. (2) For the LEV group, we will prophylactically administer 1000 mg of LEV per day to patients from the first day of admission in addition to standard stroke treatment. The LEV treatment duration will be 3 months. (3) For the PER group, we will prophylactically administer 4 mg of PER per day to patients from the first day of admission in addition to standard stroke treatment. The PER treatment duration will be 3 months. (4) After the patient is discharged from the hospital, their respective medication will be administered orally for up to 3 months. (5) All patients will receive follow-up for 18 months, and the incidence of late-onset epilepsy will be documented. Seizure characteristics, including semiology, frequency, and severity, will be analyzed in the 3 groups. The relationship of seizure semiology to stroke-related localization will be verified. (6) For those who have acute seizures during hospital admission, unblinding will be performed, and either LEV or PER will be administered for treatment according to their group. The dosage will be adjusted according to real clinical needs. These patients will be treated as having epilepsy based on the 2016 definition of epilepsy [41] and be maintained on LEV or PER after hospital admission. The administration of LEV or PER to patients with acute seizures will still be considered prophylactic therapy because patients with acute seizures have a considerably higher risk of developing poststroke epilepsy. (7) Because up to 20% of patients with anterior circulation ischemic stroke may experience electrographic seizures during the acute stage of stroke without clinically overt seizures [42], we will arrange 1 routine electroencephalogram (EEG) at the acute stage for each patient. Prophylactic AED therapy will be administered according to the group the patient is allocated to if any electrographic seizure, including periodic lateralized epileptiform discharge (PLED), is identified in the EEG. (8) Unblinding will be implemented at 3 months, and the final analysis will be conducted at 18 months.

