## Discussion

### Principal Findings

Although reports have not supported the role of prophylactic AEDs in the prevention of poststroke seizure because of a lack of randomized control trials, a lack of detected early clinical biomarkers, and worse outcomes with traditional AEDs, we will document the potential prophylactic effect of LEV and PER on poststroke seizures and epilepsy in patients with MCA infarct in this randomized clinical trial and determine the antiepileptogenic potential of LEV and PER in patients with major ischemic stroke in terms of seizure frequency and severity. We will also evaluate the safety and tolerability of these prophylactic treatments. This study will influence both stroke and epilepsy care considerably, including by potentially reducing long-term care costs and enhancing the quality of life of stroke survivors.

In addition to LEV, previous studies, including our own, have identified PER as a new AED with potential antiepileptogenic properties, attributed to its unique postsynaptic AMPA antagonism [32,38,39]. While it is not yet approved as a first-line treatment for focal epilepsy in many countries, this medication has potential and could be used at an early stage if our study confirms its effectiveness in prophylaxis against poststroke epilepsy.

The administration of AED or placebo for a period of 3 months is intended to intervene in the epileptogenesis phase, based on the relative duration of this phase observed in animal studies. Typically, the epileptogenesis phase in animal studies lasts for around 1 week, although this can vary depending on the animal model of seizure and epilepsy following brain injuries. By extrapolating from rat studies to human years [44], it is estimated that the epileptogenesis phase in rats is similar to around 3-4 months of human life. For the purposes of clinical feasibility, we administer a 3-month duration of AED.

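### The 18-month incidence pools seizures during and after dosing, so it can support a prevention claim but not, by itself, the antiepileptogenic conclusion

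*Protocol article*

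**What the plan says.** **Outcome.** Under Outcome Measures, Primary Outcome: "The primary outcome measure will be the incidence of poststroke epilepsy and seizure severity at the end of the study period", analysed by intention to treat. The Abstract (Results) gives it as "the incidence of poststroke epilepsy in the 3 groups following the 18-month study period".

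**Dosing and follow-up.** The Abstract (Methods) says of the study drug: "This treatment will continue for 12 weeks after allocation". Intervention, item 5, says: "All patients will receive follow-up for 18 months, and the incidence of late-onset epilepsy will be documented". Table 1 records seizure occurrence from the first visit to month 18.

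**Acute seizures.** Intervention, item 6, says of participants with acute in-hospital seizures: "These patients will be treated as having epilepsy based on the 2016 definition of epilepsy". Those in the active arms stay on their assigned drug. Under item 1, placebo participants who have an acute seizure are put on other antiseizure drugs and kept on them. Procedure and Assessment, by contrast, uses the baseline EEG to exclude participants with early or concurrent seizures.

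**Claim.** The Discussion (Principal Findings) explains the dosing period: "The administration of AED or placebo for a period of 3 months is intended to intervene in the epileptogenesis phase". The Abstract (Conclusions) aims to "explore the antiepileptogenic potential of both LEV and PER". Principal Findings and the closing Conclusions go further and speak of determining that potential. Yet Concept of Epileptogenesis says that antiseizure drugs "may prevent the recurrence of seizures but do not cure epileptogenesis".

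**The concern.** The article itself distinguishes two effects: holding seizures down while the drug is taken, and changing the process that leads to epilepsy. A short course followed by a long period after the drug is a sensible design for telling them apart. The stated outcome does not use that feature, because it counts events over the whole 18 months. A drug that only suppressed seizures during dosing, and left the later risk unchanged, could still show a lower 18-month incidence.

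Time to first seizure, a secondary outcome, has the same weakness because its clock also runs through the dosing period. What is at stake is the meaning of a favourable result: it could be reported as antiepileptogenic when the data show seizure prevention only.

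**Working it through.** The article gives no figure for the share of events expected during dosing, so there is none to reproduce. The checks below ask how far suppression alone could move the outcome.

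**1. Is there any off-drug restriction?** No stated washout, landmark or off-drug window applies to the primary outcome. The nearest limit is the term late-onset epilepsy in Intervention, item 5. The Introduction (Background) defines late seizures as those after day 14. Dosing lasts 12 x 7 = 84 days, so even that cut leaves about days 15-84 on drug.

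**2. Formula.** Let f be the share of placebo-arm 18-month events that fall in the dosing period, and s the proportion of these that the drug suppresses. With no effect after stopping and no re-emergence, the apparent risk ratio is 1 - f x s.

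**3. Annual risks** (Discussion, Principal Findings: 6.3% in year 1, 2.4% in year 2). Assume even risk within each year.
- 18-month risk: 6.3% + 2.4%/2 = 7.5%.
- Risk in the first 3 months: 6.3%/4 = 1.575%.
- f = 1.575/7.5 = 0.21.
- s = 0.5 (assumption): 1 - 0.21 x 0.5 = 0.895, about 0.90.
- s = 1.0 (assumption): 1 - 0.21 = 0.79.

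**4. Early and late seizure ranges** (Introduction, Background: early 2.4%-5.4%, late 7%-18%). Take the early share as a rough stand-in for f, and pair the ranges crosswise because nothing ties low to low.
- Smallest share: 2.4/(2.4 + 18) = 0.12.
- Largest share: 5.4/(5.4 + 7) = 0.44.
- s = 0.5 to 0.7 (assumption): from 1 - 0.12 x 0.5 = 0.94 to 1 - 0.44 x 0.7, about 0.70.

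This proxy is crude. It covers the first 1-2 weeks rather than 12, it may include seizures before enrolment, and the late range is not tied to 18 months.

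**5. Counting after the drug stops.** In the scenario of step 3, first seizures after dosing have a risk of 7.5% - 1.575% = 5.925% in every arm, so their risk ratio is 1.0 by construction. If instead every suppressed seizure re-emerges by month 18, the whole-period ratio also returns to 1.0.

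**6. Events available.** With 180/3 = 60 per arm (equal allocation assumed), the placebo arm expects 60 x 0.075 = 4.5 events in total and 60 x 0.05925, about 3.6, after dosing.

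**7. Chance of a significant result from suppression alone.** At 60 per arm, over placebo risks of 7%-18%, f of 0.1-0.5 and s of 0.5-1.0 (all scenario values), the chance of P<.05 in favour of the drug is about 3%-30%. The main problem is therefore what the estimate means, more than a high chance of a spurious significant finding.

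**The case against.** The strongest reply is that the outcome fits the stated objective. The Abstract (Objective) asks whether early treatment lowers the risk of developing poststroke epilepsy, and whole-period incidence by intention to treat answers that. This stands, and it limits the point to the antiepileptogenic reading.

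Second, about 15 of the 18 months follow the planned end of drug, and the Discussion puts the peak of late seizures at 6-12 months. A participant whose epileptogenesis is unaltered has ample time to seize later. This also stands: the distortion is partial and could be small.

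Third, the seizure times needed for a split are already recorded, and an analysis plan not shown here may use them. That is fair as to detail. But the article does fix the outcome, its time point and the intended conclusion, and the first two do not carry the third.

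A reader might also infer from item 6 that acute in-hospital seizures count as primary events. The text does not settle this. The sentence sits in a description of drug administration. The next one still calls the treatment prophylactic because such participants are at higher risk of poststroke epilepsy, which suggests that the endpoint has not yet been reached. Procedure and Assessment would exclude early seizures altogether.

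**Conclusion.** The point holds in a limited form. As stated, the primary outcome supports a conclusion about preventing poststroke epilepsy over 18 months. It does not by itself support a conclusion about antiepileptogenic potential.

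Suppression alone could produce an apparent risk ratio of about 0.79-0.90 on the annual risks, or about 0.70-0.94 on the early and late ranges. Both rest on assumed suppression and no re-emergence, and the first also on even risk within years. The article fixes neither the on-drug share nor the degree of suppression, so these are illustrations of scale, not predictions.

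It would go too far to say that the primary outcome is wrong for the trial, or that a favourable result would be wholly suppression. The documents support neither.

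**What to change.** 1. Keep the 18-month incidence as the outcome for the prevention claim.
2. Prespecify a second comparison: the proportion with any unprovoked seizure or epilepsy after the planned end of study drug. Use all randomised participants as denominator, because restricting to those seizure-free at 3 months would break the randomised comparison. Report events during dosing separately by arm.
3. State how participants kept on antiseizure drugs after an acute seizure (Intervention, items 1 and 6) are handled in that comparison. For them the later period is not drug-free in any arm.
4. Reconcile Intervention with Procedure and Assessment on whether participants with acute or electrographic seizures are excluded or kept, and say whether those seizures are endpoint events.
5. Reserve the term antiepileptogenic for a lower rate of events arising after the drug stops. A cumulative gap made during dosing and merely carried forward to month 18 does not qualify, since pure suppression would produce it. Otherwise conclude seizure prevention only.

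The cost is one added analysis of seizure times already collected, plus a stricter conclusion. It should be fixed in writing before group-level results are seen: Intervention, item 8, unblinds at 3 months, so a split chosen later could be challenged as data-driven. The real downside is precision. With perhaps 3 to 4 post-dosing events expected in the placebo arm on the annual risks, the result should be given as an estimate with its confidence interval, and the absence of a significant difference should not be read as absence of effect.

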**Objective:**

This research protocol is designed to conduct a randomized controlled trial to assess whether the early, preventive introduction of low-dose antiepileptic drug therapy (levetiracetam [LEV] or perampanel [PER]) in patients who have experienced middle cerebral artery (MCA) infarction can reduce the risk of developing poststroke epilepsy (primary prevention).

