### Statistical Analysis

Continuous variables will be assessed using a 2-tailed *t* test or ANOVA, followed by the Fisher least significant difference test. When data are not normally distributed, analyses will be performed using the nonparametric ANOVA Kruskal-Wallis H test followed by Dunn multiple comparison test for nonrepeated measures and the Friedman test for repeated measures. ANOVA will be used where sessions or quadrants will be treated as a within-subject factor and groups as a between-subjects factor. Analyses will be performed using a chi-square test, Yates chi-square test, or Fisher exact test for nominal variables. Differences will be considered statistically significant at a *P* value <.05, and actual *P* value will be reported, unless *P*<.001.

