### Conclusions

We anticipate that the intervention group will experience a lower incidence and severity of poststroke epilepsy than the control group. We will be able to document the potential prophylactic effect of LEV and PER in poststroke seizures and epilepsy in patients with MCA infarct and determine the antiepileptogenetic potential of LEV and PER in patients with major ischemic stroke.

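### The stated primary test compares all three arms at once, while the trial's question is each drug against placebo, and no drug-placebo contrast is named as deciding it

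*Protocol article*

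**What the plan says.** - **Primary comparison** (Outcome Measures, Primary Outcome): "Univariate ANOVA of the LEV, PER, and placebo groups will be performed". No other primary comparison is given. The abstract's Results paragraph also names no contrast: "The primary outcome under evaluation will be the incidence of poststroke epilepsy in the 3 groups following the 18-month study period".
- **Status of drug against drug** (Abstract, Results): "Exploratory outcomes will involve comparing the effectiveness and safety of PER and LEV".
- **Question and expected answer.** The abstract's Objective asks whether early low-dose LEV or PER lowers the risk of poststroke epilepsy. The abstract's Conclusions state: "We anticipate that the intervention groups will experience a lower incidence and reduced severity of poststroke epilepsy compared to the control group after 18 months". The Conclusions of the Discussion state: "We anticipate that the intervention group will experience a lower incidence and severity of poststroke epilepsy than the control group". Both set treatment against control.
- **Follow-up tests** (Statistical Analysis). Fisher's least significant difference (LSD) follows a t test or ANOVA, in a sentence about continuous variables; Dunn's test follows Kruskal-Wallis for non-normal data. For categorical outcomes the text is: "Analyses will be performed using a chi-square test, Yates chi-square test, or Fisher exact test for nominal variables". That sentence names no pair of arms, order or gate. Significance is P<.05 throughout.
- **Size** (Methods, Overview; Randomization and Blinding): 180 patients in three equal groups. The sample-size calculation is for 3 groups and names no contrast.

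**The concern.** An omnibus test asks whether the three arms are all alike. The trial asks whether a given drug does better than placebo. The two answers can differ in both directions:

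- The omnibus can be non-significant although one drug is significantly better than placebo, because the single-drug effect is judged within a 2-degree-of-freedom test.
- The omnibus can be significant because LEV and PER differ from each other, a comparison that the protocol itself ranks as exploratory.

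In either case a reader could not tell from the stated primary result whether prevention had been shown, or for which drug. The choice of contrast would then fall to whoever writes the report. The Intervention section has treatment unblinded at 3 months and the final analysis at 18 months, which is a further reason to have that choice fixed in writing.

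**Working it through.** **Inputs.** Arm size 180/3 = 60, before any loss (Methods, Overview; Randomization and Blinding). Alpha .05 (Statistical Analysis). The protocol gives no event rates for the design. The Introduction's background range for late seizures, 7%-18%, is used as the assumed placebo range. The drug rates and event counts below are assumptions for illustration.

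**The plan's own figure.** The only design figure is the G*Power range of 51 to 120 patients. The stated inputs (power 0.5, correlation 0.05) give 21 and 45 for a between-group test with 3 groups and 2 measurements; 51 and 120 come out with power 0.8 and correlation 0.5. That mismatch is a separate matter. On either set of inputs the calculation that fits is for an omnibus between-group test, so it does not supply the missing contrast.

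**Formula.** For arms of equal size 60 with event counts e and mean count m over the arms compared, Pearson chi-square is

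X² = Σ(e − m)² / [m(1 − m/60)], with df = number of arms − 1.

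**Example A: 11/3/7 events (placebo/LEV/PER).**
- Omnibus: m = 7; X² = (16 + 16 + 0)/(7 × 0.8833) = 32/6.183 = 5.175 on 2 df, P=.075 (one-way ANOVA on 0/1 data: .076).
- LEV versus placebo: m = 7; X² = (16 + 16)/6.183 = 5.175 on 1 df, P=.023 (Yates .047, Fisher exact .043).
- PER versus placebo: m = 9; X² = (4 + 4)/(9 × 0.85) = 1.046, P=.31.

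The first two statistics are identical. Only the degrees of freedom turn a significant drug-placebo difference into a non-significant primary result.

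**Example B: 7/2/12.**
- Omnibus: m = 7; X² = (0 + 25 + 25)/6.183 = 8.086 on 2 df, P=.018 (ANOVA .017).
- LEV versus placebo: m = 4.5; X² = 12.5/(4.5 × 0.925) = 3.003, P=.083.
- PER versus placebo: m = 9.5; X² = 12.5/(9.5 × 0.8417) = 1.563, P=.21.
- LEV versus PER: m = 7; X² = 50/6.183 = 8.086 on 1 df, P=.0045.

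Here the whole omnibus statistic is the exploratory contrast. ANOVA and chi-square agree in both examples, so the point does not depend on which of them is used for a binary outcome.

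**How often** (simulated trials, 60 per arm, Pearson chi-square, .05 per test):

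| Assumed true rates, placebo/LEV/PER | Omnibus non-significant, a drug beats placebo | Omnibus significant, neither drug differs from placebo |
|---|---|---|
| 18/9/9% | 11.7% | 0.15% |
| 18/6/12% | 14.3% | 1.0% |
| 18/6/18% (PER inert) | not tabulated | 7.0% |
| 12/4/20% (opposite effects) | not tabulated | 19% |

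**Type I error with no effect in any arm** (incidence 7/12/18%, 200,000 trials each):
- Either drug-placebo test at .05, read only after a significant omnibus: 3.7/4.1/4.3%.
- Either drug-placebo test at .05, with no gate: 8.6/8.8/8.8%. Counting only false claims of benefit: 4.4/4.5/4.4%.
- Holm on the two contrasts: 3.7/4.5/4.8%.

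**The case against.** **Omnibus followed by pairwise tests is a recognised procedure for three arms.** If the primary test is ANOVA, the Statistical Analysis section attaches LSD to it, and with three groups this holds the family-wise error near 5%. That stands as far as error control goes. It does not cure the mismatch with the objective: LSD treats all three pairs alike, LEV versus PER alone can open the gate (Example B), and the gate can stay shut when one drug beats placebo (Example A). The LSD sentence is also written for continuous variables, which yes/no incidence is not.

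**An analysis plan or full protocol, not shown, may list the contrasts.** It may, and the absence of a post-hoc rule for categorical data is not held against the article. The point is what the article does fix: the primary comparison, as a test that does not match the trial's own question.

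**Stronger readings that a reader might infer, and that the documents do not support:**
- *The false-positive rate is nearly double the nominal level.* The 8.6-8.8% needs two ungated drug-placebo tests, a procedure the protocol does not state. Even then a false claim of benefit occurs in only about 4.5%.
- *A significant primary result will often be due to the drugs differing from each other.* The 19% needs one drug to help and the other to harm. The protocol expects lower incidence on treatment, and under that expectation the figure is 1% or less.
- *The singular noun in the Discussion's Conclusions announces a pooled-drug analysis.* The Methods describe three separate groups throughout. It is loose wording, worth aligning, and not a rival primary contrast.

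**Conclusion.** The concern holds in a limited form. The protocol fixes an undirected three-group test as its only primary comparison, its objective and expected conclusion are drug versus placebo, and no such contrast is named as deciding the trial. The practical loss is mainly in one direction: with 60 per arm and assumed rates from 18/9/9% to 18/6/12%, the stated primary test is non-significant while a drug beats placebo in about 11-15% of trials. The opposite failure is 1% or less if both drugs help, 7% if one is inert, and larger only if they act in opposite directions. Inflation of the type I error is conditional and is not shown by what the protocol states. All sizes rest on assumed event rates, equal arms without loss, and Pearson chi-square. The mismatch itself rests on the text alone. The joining of seizure severity to incidence ("The primary outcome measure will be the incidence of poststroke epilepsy and seizure severity at the end of the study period") and the use of ANOVA for a binary outcome are separate points on which this one does not depend.

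**What to change.** In Outcome Measures, Primary Outcome, replace the ANOVA sentence with wording to this effect: *The primary comparisons for 18-month incidence of poststroke epilepsy are LEV versus placebo and PER versus placebo, each two-sided, with family-wise error controlled at .05 by the Holm procedure. Success for a drug is claimed only from its own comparison with placebo.* Report the three-group omnibus test as supportive, and keep LEV versus PER as an exploratory estimate with a confidence interval. Align both Conclusions passages to *each intervention group*. Date the change and make it before incidence is seen by arm.

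**Cost.** No extra patients or data. Under Holm the smaller of the two P values must be below .025. At assumed rates of 18/6/6%, the chance that at least one drug succeeds is about 57%, against 59% for a significant omnibus. In return, each success belongs to a named drug.
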